## Abstract

**Background:**

Cystic fibrosis (CF) is a rare, inherited, life-limiting condition predominantly affecting the lungs, for which there is no cure. The disease is characterized by recurrent pulmonary exacerbations (PEx), which are thought to drive progressive lung damage. Management of these episodes is complex and generally involves multiple interventions targeting different aspects of disease. The emergence of innovative trials and use of Bayesian statistical methods has created renewed opportunities for studying heterogeneous populations in rare diseases. Here, we present the protocol for the BEAT CF PEx cohort, a prospective, multi-site, perpetual, platform enrolling adults and children with CF. The BEAT CF PEx cohort will be used to evaluate the comparative effectiveness of interventions for the treatment of PEx requiring intensive therapy (PERITs), with a primary focus on short-term improvements in lung function. This will be achieved through the conduct of cohort-nested studies, including adaptive clinical trials, within the BEAT CF PEx cohort. This protocol will outline key features of the BEAT CF PEx cohort, including the design, implementation, data collection and management, governance and analysis, and dissemination of results.

**Methods:**

This platform will be conducted across multiple sites, commencing with CF treatment centers in Australia. People of all ages with a clinical diagnosis of CF will be eligible to participate, except those who have previously received a lung transplant. Data including demographic and clinical information, treatment details, and outcomes (including safety, microbiology, and patient-reported outcome measures including quality of life scores) will be systematically collected and securely stored via a digital centralized trial management system (CTMS). The primary endpoint is the absolute change in the percentage predicted forced expiratory volume in 1 s (ppFEV_1_) from the commencement of intensive therapy to 7 to 10 days afterwards.

**Discussion:**

The BEAT CF PEx cohort will report clinical, treatment, and outcome data for PEx among people with CF and is intended to serve as a core (master) protocol for future nested, interventional trials evaluating treatment(s) for these episodes. The protocols for nested sub-studies are beyond the scope of this document and will be reported separately.

**Trial registration:**

ANZCTR BEAT CF Platform – ACTRN12621000638831. Registration date: Sept. 26, 2022.

**Supplementary Information:**

The online version contains supplementary material available at 10.1186/s13063-023-07076-8.

## Administrative information

Note: the numbers in curly brackets in this protocol refer to SPIRIT checklist item numbers. The order of the items has been modified to group similar items (see http://www.equator-network.org/reporting-guidelines/spirit-2013-statement-defining-standard-protocol-items-for-clinical-trials/).

## Introduction

### Background and rationale {6a}

Cystic fibrosis (CF) is an inherited, life-limiting disease affecting multiple organs, predominantly the lungs. Pulmonary exacerbations (PEx) are a hallmark of disease and are thought to drive progressive lung damage; it is estimated that a quarter of people fail to fully recover lung function after these episodes [1]. While there is no consensus definition for PEx [1], episodes generally involve a deterioration in lung function and new or worsening respiratory and systemic symptoms. Management of PEx is complex, invasive, and often requires prolonged hospitalization [2]. While the use of intravenous antibiotic therapy is a cornerstone of management during hospitalization, the approach is generally multimodal and involves one or more of intensified airway clearance therapies via physiotherapy with or without muco-active agents, immune modulation, optimization of nutrition, and psychosocial support [2–6]. Important knowledge gaps remain regarding the optimal management of these episodes, and these gaps drive variations in care for people with CF both within and between centers. Management of PEx has been identified as a research priority among people with CF [7].

Randomized controlled trials are rightfully considered the gold standard for generating evidence to inform clinical practice and policy [8]. However, traditional trials can be burdensome, inefficient, and limited to addressing just one management question at a time. Trials that are burdensome (for participants or clinicians) might inadvertently select for a non-representative study population, meaning any results may not be generalizable. This presents challenges for evaluating complex and multi-component interventions in a highly heterogeneous patient population.

Newer approaches to clinical research offer an opportunity to generate high-quality evidence for guiding patient management, including in complex and rare diseases. These innovations, including nesting of studies within registries or large cohorts, pragmatism and healthcare embedding, and outcome or response-adaptation, focus on informing real world decision-making, may be more conducive to high levels of participation, and may offer greater flexibility and statistical efficiency than traditional clinical trials [9, 10]. Such approaches enable multiple treatment questions to be addressed concurrently or sequentially, according to research priorities and prespecified protocol adaptation rules [9].

Here, we present a core protocol for studying the management of PEx in the BEAT CF (Bayesian Evidence Adaptive Treatment for people with Cystic Fibrosis) platform. The PEx core protocol sets out the establishment of a prospective, multi-site cohort designed to perpetually enroll and follow-up people with CF and systematically capture data on the management and outcomes of any PEx requiring intensive therapy (PERIT). Here, a PERIT is pragmatically defined as an acute or subacute deterioration in lung function or symptoms resulting in (possibly multimodal) therapy comprising initiation of at least one intravenous antibiotic. It is anticipated that most cohort participants will become eligible to participate in cohort-nested sub-studies, including a PEx Treatment Platform in which selected aspects of PERIT management will be randomly assigned.

The protocol documentation for BEAT CF is modular and hierarchical (Fig. 1) to facilitate nesting of the PEx Treatment Platform and other cohort-nested sub-studies, to minimize redundancy in the documentation, and to maximize consistency and standardization across the cohort and any nested projects. Here, we describe the core objectives, endpoints, data collection, and study procedures for the PEx cohort, along with plans for the analysis and reporting of their data. All current approved versions of the BEAT CF protocol documentation are available at https://www.beatcf.org.au/beat-cf/.

**Fig. 1 Fig1:**
[figure not shown]
BEAT CF protocol documentation for the BEAT CF PEx cohort and related and nested sub-studies

### Objectives {7}

The primary objective of the PEx cohort is to identify the effectiveness, or comparative effectiveness, of alternative interventions that are currently in routine use, or proposed for future use, in the management of PERITs in children and adults with CF, with respect to short-term improvements in lung function. For the purpose of the PEx cohort, “intensive therapy” means therapy comprising the initiation of at least one antibiotic by the intravenous route.

Secondary objectives are to identify the effectiveness, or comparative effectiveness, of alternative interventions on:Long-term improvements in lung functionShort and long-term improvements in symptoms, quality of life (QoL) and life expectancyShort and long-term healthcare utilization, including for management of PERITsThe toxicity and comparative toxicity of alternative interventionsThe cost-effectiveness of alternative interventionsThe impact of alternative interventions on the generation or selection of antibiotic resistant bacteria and the impact of this on lung function and QoL

### Trial design {8}

The PEx core protocol describes the establishment of a prospective, multi-site cohort that is intended to perpetually enroll children and adults with CF to serve as an adaptive platform for evaluating the (comparative) effectiveness of interventions for PEx, including through cohort-nested sub-studies. The PEx cohort is intended to be representative of the total CF population (Fig. 2). The PEx cohort will collect data regarding participant and disease characteristics, details of PERIT management, and clinical outcomes to identify, explain and quantify differences in treatment outcome(s) among people with CF treated for PEx.

**Fig. 2 Fig2:**
[figure not shown]
The relationship between the BEAT CF cohort and nested substudies

## Methods: participants, interventions, and outcomes

### Study setting {9}

The PEx cohort enrolls participants from CF treatment centers, comprising hospitals, their regional outreach clinics, and ambulatory care facilities. While enrolment is currently limited to Australian centers, the protocol permits extension to international sites. The addition of new sites is contingent upon the successful completion of a site feasibility assessment. All project staff are required to undergo good clinical practice training and project-specific training prior to their involvement. As of August 2022, ten Australian sites are participating. An updated list of participating sites is available on the study website located at https://www.beatcf.org.au/beat-cf/.

### Eligibility criteria {10}

All children and adults with a confirmed diagnosis of CF are eligible for inclusion in the PEx cohort, excluding those with a history of lung transplantation. Additional eligibility criteria (typically exclusion criteria) may apply to cohort-nested sub-studies, and these will be detailed in their relevant subprotocols or appendices. Co-enrolment of participants in other studies is permitted, whether they are formally nested in the PEx cohort or not, including interventional trials, except when there is a clear threat to the validity of either study, or where co-enrolment would materially influence the risk to participants.

### Who will take informed consent? {26a}

Informed consent for participation in the PEx cohort is obtained by authorized project staff. Electronic and/or written versions of the participant information sheet and consent form will be presented to the participant and/or legal guardian detailing background information about the project, requirements of participants, potential risks, and the anticipated outcomes and constraints. Participation will be voluntary and will not impact on patient care. Participants will be free to terminate their involvement at any stage. Consent via written or electronic signature will be required from the participant and/or legal guardian prior to inclusion.

### Additional consent provisions for collection and use of participant data and biological specimens {26b}

As the PEx cohort is designed to be perpetual, participant consent will be regularly assessed to ensure it is appropriate and current. When a participant turns 18 years old, they are invited to provide informed consent as an adult. Children under 18 years old may provide their own consent, in consultation with their legally responsible caregiver. No additional investigations (including laboratory or radiological tests) outside of routine care are performed for the PEx cohort but may be required by participation in a nested sub-study. Participation in any nested studies is voluntary, and any additional procedures beyond routine care will require additional consent.

### Interventions

#### Explanation for the choice of comparators {6b}

The PEx cohort is observational; therefore, no specific interventions are defined for this cohort. For the purpose of reporting a sub-study from the PEx cohort, a PERIT intervention is considered to be any treatment, procedure, or strategy used in the acute management of a PERIT. PERIT interventions in the sub-studies are grouped into therapeutic domains comprising sets of mutually exclusive interventions, for example, sets of backbone antibiotics, sets of adjunctive antibiotics, sets of mucolytic therapies, sets of alternative physiotherapeutic regimens, and sets of immunomodulator treatments.

#### Intervention description {11a}

Participants in the PEx cohort receive usual care in each therapeutic domain as directed by their treating medical team, except as required by participation in a nested sub-study where certain interventions may be assigned. Any assignment of interventions and their relevant comparators will be specified in the relevant subprotocols or appendices for those sub-studies. All current approved versions of the BEAT CF protocol documentation are available at https://www.beatcf.org.au/beat-cf/.

#### Criteria for discontinuing or modifying allocated interventions {11b}

Participants in the PEx cohort may discontinue or modify one or more PERIT intervention(s) at any time in consultation with their treating clinician, except as required by participation in a nested sub-study. They may also discontinue from the PEx cohort entirely if (i) they and/or their legal guardian requests withdrawal or (ii) their treating medical team decides continued participation is not in their best interests. Consent to the use of study data, including data collected until the time of discontinuation and data to inform primary and secondary outcomes, will be requested specifically from participants or their legal representative. Following discontinuation, participants will receive all care as directed by their treating medical team. Any procedures for withdrawal from or modification of any assigned interventions will be specified in their relevant subprotocols.

#### Strategies to improve adherence to interventions {11c}

As the PEx cohort is observational, no specific strategies will be used to ensure adherence to prescribed therapies. Any strategies used to improve adherence to any assigned interventions in sub-studies will be detailed in the relevant subprotocols.

#### Relevant concomitant care permitted or prohibited during the trial {11d}

All PERIT management decisions are at the discretion of the treating clinician, except as required by participation in a nested sub-study. Any prohibited interventions will be specified for participants in the relevant subprotocols or appendices. Data regarding interventions, including concurrent therapies are recorded.

#### Provisions for post-trial care {30}

Participants in the PEx cohort will receive usual care for each PERIT and between PERIT episodes, except as required by participation in any nested sub-studies. Any procedures for post-intervention sub-study care will be specified in the relevant subprotocols.

#### Outcomes {12}

The primary estimand (inferential target for estimation) for each participant, for each PERIT, is defined by:*Study population:* People with CF with a PERIT who can perform spirometry and for whom there is reasonable equipoise about the most appropriate first line treatment regimen*Primary outcome and endpoint:* The change in lung function 7–10 days after commencing intensive therapy (therapy entailing use of at least one intravenous antibiotic), measured as the absolute change in percentage predicted forced expiratory volume in 1-s (ppFEV_1_) from initiation of intensive therapy (measured closest in time to the first dose on IV therapy, *and not* ≥ 14 days before, *and not* ≥ 72 hours afterwards) to the first measured ppFEV_1_ ≥ 7 days afterwards (measured closest in time to 7x24 hours afterwards *but not* ≥ 10 days (10x24 hours) afterwards)*Primary effect measure:* The absolute difference in the mean of the primary endpoint between those in the intervention versus the comparator group, adjusting for any differences in baseline factors between intervention and comparator arms that might otherwise confound or reduce the certainty of the treatment effect*Interventions:* Prescription of each intervention within a domain*Comparators*: Prescription of each other Intervention within that domain*Intercurrent events:* Participants will be included in the primary analysis irrespective of whether and how the intervention or comparator is received, any non-adherence, any subsequent change in therapy, or loss to follow-up, (i.e., the effect attributable to the prescription, or the treatment policy or de facto estimand)

For each PERIT, we will also report the following outcomes measured as the following endpoints:The change in lung function up to 6 months after commencement of intensive therapy, *measured as* the absolute change in the ppFEV_1_ from initiation of intensive therapy until approximately 14 days (≥ 14 days to < 30 days), 30 days (≥ 30 days to < 60 days), 60 days (≥ 60 days to < 90 days), and 180 days (≥ 180 days to < 240 days) after commencement of intensive therapyThe change in lung function up to 6 months after commencement of intensive therapy, *measured as: (i)* the proportional change (expressed as a percentage) in the ppFEV_1_ from initiation of intensive therapy until 7 days (≥ 7 to < 10 days), 14 days (≥ 14 days to < 30 days), 30 days (≥ 30 days to < 60 days), 60 days (≥ 60 days to < 90 days), and 180 days (≥ 180 days to < 240 days) after commencement of intensive therapy; (ii) the return of measured lung function to close to its baseline (pre-exacerbation) best function, up to 6 months after commencement of intensive therapy, *measured as* a binary outcome of whether the ppFEV_1_ has returned to ≥ 90% of the ppFEV_1_ at baseline, at approximately 7 days (≥ 7 to < 10 days), 14 days (≥ 14 days to < 30 days), 30 days (≥ 30 days to < 60 days), 60 days (≥ 60 days to < 90 days), and 180 days (≥ 180 days to < 240 days) after commencement of intensive therapy, where the baseline ppFEV_1_ is the highest recorded ppFEV1 in the 180 days (or 365 days if no ppFEV_1_ < 180 days) preceding the commencement of intensive therapyThe change in CF-related symptoms up to 4 weeks after commencement of intensive therapy, *measured as* the absolute change in the Chronic Respiratory Infection Symptom Score (CRISS) score approximately 7 days (≥ 7 to < 10 days), 14 days (≥ 14 days to < 30 days), 30 days (≥ 30 days to < 60 days), after commencement of intensive therapyThe time to the next PERIT, *measured as* the time (in days) from commencement of intensive therapy to the next commencement of intensive therapy, after a period of no intensive therapy of ≥ 7 daysAdverse reactions resulting in treatment cessation, *measured as* any early termination of planned therapy before 7 days (7*24 hours) and before 14 days (14*24 hours) after commencement of intensive therapy, owing to one or more adverse events presumed by the responsible clinician to be attributable to the prescribed therapyTreatment failure resulting in treatment cessation, *measured as* any early termination of planned therapy before 7 days (7*24 hours) and before 14 days (14*24 hours) after commencement of intensive therapy, owing to inadequate improvement in symptoms or lung function, presumed by the responsible clinician to be attributable to a poor response to the prescribed therapy

Note that additional outcomes (including safety outcomes) may apply to cohort-nested sub-studies, and these will be detailed in their relevant subprotocols.

For all participants, we will also report:The Cystic Fibrosis Questionnaire-revised (CFQR) score approximately every 12 weeks for all participants ≥ 6 years oldAny new detection of any strain of gram-negative bacteria with in vitro resistance to any aminoglycoside, fluoroquinolone, antipseudomonal penicillin (including beta-lactam/beta-lactamase inhibitor combination), antipseudomonal cephalosporin, or carbapenem not previously detected since enrolment in the PEx cohort or in the 2 years priorAny new onset of *Clostridium difficile* associated diarrhea not previously detected since enrolment in the PEx cohort or in the 2 years prior

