	Date and details of any new, documented infection, or airway colonization	Y^a^	Y	The presence of specific pathogens may influence therapeutic choices, plausibly confounds or modifies treatment effects. Selection of resistant pathogens may be an untoward outcome of antibiotic therapy
	Date and details of any new, documented infection with *Clostridium difficile*	Y^a^	Y	*Clostridium difficile*-related diarrhea is an important untoward outcome of antibiotic therapy
**Patient-reported outcomes**:	Cystic Fibrosis Questionnaire-revised (CFQ-R) for all participants ≥6 years old	Y	Y	Treatment of PEx plausibly impacts on quality-of-life (QoL) over time
**Anthropometric**	Height	Y	Y	Height is associated with FEV_1_ and is essential for estimating the ppFEV_1_
	Weight	Y	Y	Treatment of PEx plausibly impacts on weight over time
**Spirometry**	FEV_1_	Y^b^	Y	Treatment of PEx plausibly impacts on lung function. The ppFEV_1_, is strongly associated with morbidity and mortality in CF

^a^Including results in the 24 months preceding enrolment into the cohort

^b^Including results in the 12 months (365 days) preceding enrolment into the cohort

**Table 2 Tab2:** Additional outcome data for each PERIT

	Variable	Timing	Reason
**PEx therapy**	Date and time of commencing IV therapy	Day 0	As a time reference point for analyses
**PEx therapy**	Location (hospital or HITH)	Daily	For description of the cohort. Location may constrain therapeutic options and plausibly confound or modify treatment effects
**Spirometry**	FEV_1_	Days 0 (at admission), 7, 14, 30, 60, and 180	Treatment of PEx plausibly impacts on lung function, measured as ppFEV_1_; this is strongly associated with morbidity and mortality in CF
**Clinical assessment**	Presence and quality of cough	Daily	Reduction in cough and/or improvement in cough quality are measures of successful treatment of PEx
	Presence of crepitations	Daily	Reduction in crepitations is a measure of successful treatment of PEx
**Patient-reported outcomes**	CRISS score (if > 12 years at admission)	Day 0: as close as practicable to the initiation of IV antibiotics, and not > 72 h afterwards, then days 7, 14, and 30	CRISS is a validated measure of CF-related symptoms in the preceding 24 h. It is expected that successful treatment will result in an improved CRISS score. It will be used to assess clinical response to treatment for PEx

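### The baseline spirometry look-back (under 14 days) is longer than the 7-day IV-free gap that separates PERITs, so a reading from the previous IV course can become the next episode's starting value

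*Protocol article*

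**What the plan says.** All references are to the Protocol article.

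- **Unit of analysis.** Outcomes {12} defines "The primary estimand (inferential target for estimation) for each participant, for each PERIT", so successive episodes in one person each count.
- **Starting value.** The same section takes the reading "measured closest in time to the first dose on IV therapy, *and not* ≥ 14 days before", and on the other side "and not* ≥ 72 hours afterwards". It does not require the reading to fall outside an earlier IV course.
- **Follow-up value.** The change runs "to the first measured ppFEV_1_ ≥ 7 days afterwards", with an upper limit just short of day 10.
- **Separation of episodes.** In Outcomes {12}, the time-to-next-PERIT endpoint counts a new start of intensive therapy once at least 7 days have passed without it. That is the only separation rule. Background and rationale {6a} defines a PERIT as "an acute or subacute deterioration in lung function or symptoms resulting in (possibly multimodal) therapy comprising initiation of at least one intravenous antibiotic", with no minimum interval. Objectives {7} and the Discussion add none.
- **When spirometry happens.** Table 2 lists FEV1 at "Days 0 (at admission), 7, 14, 30, 60, and 180". The consent provisions in {26b} state: "No additional investigations (including laboratory or radiological tests) outside of routine care are performed for the PEx cohort".

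**The concern.** The starting value should describe the patient in the deteriorated state that led to IV treatment. The permitted look-back is up to twice the shortest interval that separates two episodes. For a PERIT starting 7 to under 14 days after the previous course ended, the window therefore reaches back into that course.

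A reading from there was taken on treatment and before the new deterioration. The Discussion says that most FEV1 recovery occurs in the first week of therapy, so a reading from after day 7 of the earlier course is likely to be close to the recovered level. Used as a starting value, it would probably understate the improvement in the new episode. The same reading may also be the outcome of the earlier PERIT, which ties the errors of the two episodes together.

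The starting value feeds the later absolute and proportional changes in ppFEV1 as well as the primary endpoint. The Discussion also says that the core primary endpoints are generic to nested sub-studies, so the rule is passed on to them.

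**Working it through.** The plan gives no figure to reproduce. The check is interval arithmetic on its stated windows.

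**Inputs from Outcomes {12}:** look-back under 14 days; look-forward under 72 hours (3 days); minimum IV-free gap 7 days; primary follow-up reading from day 7 to before day 10. Course lengths L are illustrative; the Discussion mentions 10 days of IV therapy, and the other lengths are assumed.

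**1. Overlap with the previous course.** With IV-free gap g ≥ 7, the overlap is max(0, 14 − g) days.

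| g (days) | 7 | 8 | 10 | 12 | 13 | 14 or more |
|---|---|---|---|---|---|---|
| Overlap (days) | 7 | 6 | 4 | 2 | 1 | 0 |

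**2. When an on-course reading is selected.** The closest reading wins. Take g = 7 and a reading 8 days before the new first dose, which falls within the previous course.
- If it is the only eligible reading, it is the starting value.
- If there is also a reading at day −5, day 0 or day +2.9, that one replaces it.
- A reading at exactly day +3.0 is outside the window and does not replace it.

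Selection therefore needs no spirometry for g + 3 days, running from the end of the previous course to 72 hours after the new first dose. That is 10 days at g = 7 and just under 17 days as g approaches 14.

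**3. Can the previous PERIT's primary endpoint reading be reused?** A reading on day t of the earlier course (7 ≤ t < 10) is L + g − t days old at the new start. It is eligible if L + g − t < 14, that is, if t > L + g − 14. Since t < 10, this needs L + g < 24.

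| L | g | New start (day L + g) | Eligible after day | Day 7 to <10 readings eligible |
|---|---|---|---|---|
| 10 | 7 | 17 | 3 | all |
| 10 | 10 | 20 | 6 | all |
| 10 | 13 | 23 | 9 | after day 9 only |
| 14 | 7 | 21 | 7 | after day 7 only |
| 14 | 10 | 24 | 10 | none |
| 16 | 7 | 23 | 9 | after day 9 only |
| 17 | 7 | 24 | 10 | none |

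For a 14-day course with a 7-day gap, a reading at exactly 7 × 24 hours is 21 − 7 = 14 days old and is excluded. Only a later reading qualifies.

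**4. Effect of reuse.** Let e be the measurement error in the shared reading. It enters the first episode's change as +e and the second's as −e, which contributes −Var(e) to their covariance.

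**5. Size, on assumed values only.** Suppose the on-treatment value is 70, the unmeasured value at the new IV start is 62, and day 7 of the new course gives 69. The true change is 69 − 62 = +7 and the recorded change is 69 − 70 = −1, an error of −8 points. If 2%, 5% or 10% of PERITs in one group were affected, that group's mean would shift by 0.02 × 8 = 0.16, 0.05 × 8 = 0.40 or 0.10 × 8 = 0.80 points downward. The difference between groups moves only by 8 × (difference in affected shares): zero if the shares are equal, and 8 × (0.05 − 0.02) = 0.24 points if they are 5% and 2%.

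**The case against.** The strongest reply is that several conditions must coincide. The gap must be 7 to under 14 days, and nobody may have measured FEV1 for at least 10 days spanning a deterioration serious enough to start IV antibiotics. Table 2 schedules a reading on day 0, and the closest-in-time rule prefers any nearer one. This stands: it is an edge case. It does not close the gap, because the cohort adds no tests to routine care, and a look-back of nearly 14 days itself allows for a missing day-0 reading.

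A reader might infer that the error biases treatment comparisons because early relapse depends on the first regimen. The document does not support that. The error falls in the second PERIT, which is analysed by its own initial prescription (section {20c}). Uneven error would need the affected share to differ between the second episode's groups, for example because regimens carry over, and nothing stated shows this. The effect measure is also a baseline-adjusted difference between groups, so a shift in one group's mean is not a bias in the contrast.

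It can also be said that closely spaced episodes are a derivation detail for the full protocol or the SAP, neither of which is shown. That would hold if the article were silent. Here it fixes the window to the hour, and the window as written admits on-course readings.

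Last, a reading taken just after the last IV dose is nearly as much a post-treatment value as one taken just before it. This is correct and limits what the fix can achieve.

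**Conclusion.** The point holds as a defect in a stated rule for the primary endpoint. For IV-free gaps of 7 to under 14 days, the window overlaps the previous course by up to 7 days, and an on-treatment reading is used when no nearer one exists. Reuse of the previous primary endpoint reading is possible only when course length plus gap is below 24 days. The consequence is a misstated change for that PERIT, probably too small, and sometimes an induced negative link between two episodes.

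The overlap follows from the document's own figures. The frequency does not: no data on gaps or missing day-0 readings are given, and the 8-point error and the 2%, 5% and 10% shares are assumptions. The analysis also takes the 7-day gap from a secondary endpoint. Because the PERIT definition itself sets no minimum separation, the episode boundary for the primary estimand is at least as open as assumed here. Neither a common problem nor a biased treatment contrast has been shown.

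**What to change.** Add one sentence to the primary endpoint in Outcomes {12}: the starting ppFEV1 must be measured after the last IV dose of any earlier course. The look-back then becomes the shorter of 14 days and the time since the previous intensive therapy ended, and no on-treatment reading of one PERIT can serve as the starting value of another. If no reading qualifies, treat the starting value as missing, handle it by the planned missing-data method, and keep the PERIT in the analysis.

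This needs a derivation rule using IV start and stop dates. It changes no care and adds no test. The overlap in the first table falls to 0 days for every gap.

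The cost is that a few closely spaced PERITs lose their starting value. These are early relapses, so the loss is selective, which is why they should stay in the analysis. The cure is partial: a reading taken shortly after the previous course ended, but before the new deterioration, remains eligible.
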